**(Current project) Aim 2 – To identify the combined effects of consistent and conflicting messages from different sources—including clinicians, social relationships, and media—on breast cancer screening beliefs, attitudes, and intentions over time.** Using top-rated messages from Aim 1, we will conduct a two-wave online survey experiment with 3000 older women from a nationally representative panel. The two waves will include a clinician message intended to reduce over-screening (i.e. mentions harms of over-screening, supports screening cessation) and a non-clinician message. We will vary whether the non-clinician message is from family/friend or the media; we will also vary whether the non-clinician message supports or opposes screening cessation. We hypothesize that the effect of clinician message on screening intentions will be strengthened when paired with consistent messages and weakened when paired with conflicting messages.

(Next step) Aim 3 – To engage multi-disciplinary stakeholders to devise message delivery strategy for subsequent intervention. We will conduct focus groups with 30-40 stakeholders representing the end users of the messaging strategies, including clinicians, health system administrators, older women, caregivers, community leaders, advocacy group representatives, and health journalists. Focus groups will help devise strategies to deliver, in a real-world context, the messages from Aim 2 that most effectively reduced screening intentions.

This innovative work will produce much needed data on effective strategies to communicate the rationale for stopping cancer screening when harms outweigh the benefits. The results will directly inform a novel communication intervention, as next step, to reduce breast cancer over-screening among older women.

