**C.2. Study Setting / Recruitment / Randomization / Blinding / Data collection**

We will recruit participants from the KnowledgePanel, which is a nationally representative online survey panel maintained by a survey research company Ipsos. KnowledgePanel is a largest probability-based online panel consisting of about 55,000 adult members that covers 97% of the U.S. adult population. KnowledgePanel includes good representation of older women across the spectrum of different health status. Panel members are randomly recruited by random digit dialing telephone (until 2009) or by address (since 2009); the sampling frame includes both listed and unlisted numbers and households are provided with access to internet and hardware if needed. Extensive analyses by independent researchers have consistently found the KnowledgePanel to closely match other nationally representative surveys such as the Health and Retirement Study. KnowledgePanel has been used in numerous medical research studies involving older adults, including our own prior work. Based on prior experience we expect a response rates of 65-70% among older adults who are invited to participate.

KnowledgePanel will be responsible for inviting panel members to the study via email and for programming the survey for online administration. During the survey programming, randomization will be achieved using randomly generated numbers. To ensure matched participant characteristics across groups, participants will be sorted by the randomly generated numbers and by race/ethnicity, geographic region, education (these information have already been collected by KnowledgePanel about its members), then the participants, thus sorted, will be allocated sequentially to each of the 6 experimental groups. Participants and the research team will be blinded to the allocation until data collection is complete. Only de-identified data will be sent from KnowledgePanel to the study team.

KnowledgePanel will pretest each wave of the survey with individuals not included in the study to ensure programming and randomization procedures occur as intended. Specifically, KnowledgePanel will pretest wave 1 survey with 50 eligible older women, and pretest wave 2 survey with the same individuals, recognizing that not all 50 may complete wave 2's pretest.

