**C.3. Eligibility Criteria**

- Inclusion criteria: 65 years; female; part of KnowledgePanel; able to complete survey in English.
- Exclusion criteria: personal history of breast cancer

KnowledgePanel already collects information on panel members' age, gender, English proficiency. We will independently include a screening question at the beginning of the survey regarding breast cancer history.

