### C.5. Outcomes and timeline (Table 2):

Table 2. Aim 2 study outcomes and timing of assessments.

|             | Outcomes                                                                                       | Group 1 |    | Group 2 |    | Group 3/4 |    | Group 5/6 |    |
|-------------|------------------------------------------------------------------------------------------------|---------|----|---------|----|-----------|----|-----------|----|
|             |                                                                                                | W1      | W2 | W1      | W2 | W1        | W2 | W1        | W2 |
| Primary     | Support for screening cessation for hypothetical patient                                       | x       | x  | x       | x  | x         | x  | x         | x  |
| Secondary   | Screening intention for oneself                                                                | x       | x  | x       | x  | x         | x  | x         | x  |
| Secondary   | Screening attitudes                                                                            | x       | x  | x       | x  | x         | x  | x         | x  |
| Secondary   | Awareness of harms of screening                                                                | x       |    | x       |    | x         |    | x         |    |
| Secondary   | Negative perceptions of mammograms                                                             |         |    | x       |    | x         |    | x         |    |
| Secondary   | Perceived effects on making one think more carefully or seek more information about mammograms |         |    | x       |    | x         | x  | x         | x  |
| Secondary   | Emotional response                                                                             |         |    | x       |    | x         |    | x         |    |
| Exploratory | Outcomes related to conflicting messages (confusion, backlash, ambivalence)                    | x       |    |         |    |           | x  |           | x  |
| Exploratory | Open-ended impression                                                                          |         |    | x       |    | x         |    | x         |    |

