Support for screening cessation for hypothetical patient: “How strongly do you believe that older women with a lot of health problems like [name] should get a mammogram in the next two years? Measured on a 7-point scale (1=definitely should get a mammogram; 7= definitely should not get a mammogram).

Screening intention for oneself: “How likely is it that you will get a mammogram in the next two years?” Measured on a 7-point scale (1=very likely to get a mammogram, 7=very unlikely to get a mammogram).

Attitudes:

- “For you, would you say getting a mammogram in the next two years is... 1=unimportant; 5=important; 1=harmful; 5=beneficial; 1=not worthwhile; 5=worthwhile;

- “For older women with a lot of health problems like [name], would you say getting a mammogram in the next two years is... 1=unimportant; 5=important; 1=harmful; 5=beneficial; 1=not worthwhile; 5=worthwhile;

Awareness of harms of screening: “Have you ever heard or read the following information? You could have heard or read this information during this survey or previously.” (Yes/No)

- For some women over age 65 who have a lot of health problems, medical guidelines recommend against regular mammograms.
- Mammograms can find slow-growing breast cancers that might never cause problems but can lead to unnecessary, risky treatments such as surgery or radiation.
- Mammograms can have false alarm results that may cause stress, anxiety, and require breast biopsy.

Negative perceptions of mammograms:

“Thinking about the information that was shared, please rate how much you agree or disagree with the following statement.” (1=strongly disagree; 5=strongly agree)

- This information discourages me from wanting to get a mammogram.
- This information makes getting a mammogram seem unpleasant to me.
- This information makes me concerned about the health effects of getting a mammogram.

Effect perceptions:

“Thinking about the information that was shared, please rate how much you agree or disagree with the following statement.” (1=strongly disagree; 5=strongly agree)

- This information would make me think carefully about getting a mammogram
- This information would make me want to find out more information about the potential benefits of getting a mammogram.
- This information would make me want to find out more information about the potential downsides of getting a mammogram.

Emotional response:

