#### **C.6. Statistical methods and sample size.**

The main analysis focuses on the primary outcome assessed at Wave 2 with the independent variables being the randomly assigned message/messenger combinations. The primary goal is to compare the experimental groups (Groups 3-6) at Wave 2 with both control groups to assess the combined effect of consistent and conflicting messages over time. We hypothesize that the participants who read consistent messages both directed at reducing over-screening (Groups 3,4) will have higher support and higher intentions to stop screening than participants who read clinician message alone (Group 2); the participants who read conflicting messages (Groups 5,6) will have lower intentions to stop screening than participants who read clinician message alone (Group 2). We will compare the mean scores across groups using ANOVA and adjust for multiple comparisons. We will conduct exploratory analyses by key covariates, including age, predicted life expectancy based on health and functional status, to examine the impact of messaging within these subgroups.

Power calculations are based on preliminary data in which we asked 41 patients 65+ about willingness to stop routine cancer screening if recommended by their clinician. Based on the distribution of responses from this preliminary data, we estimate that with 400 participants randomized to each group at Wave 2, we will have 80% power to detect a 0.30 point difference for the primary outcome. The survey company Ipsos that manages and maintains the KnowledgePanel affirms that, through their recruiting strategy and based on their past experience, 20% attrition or less is expected between the two waves over 1-2 weeks. Assuming 20% attrition, we will target 500 per group at Wave 1.

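### The protocol names no pre-message screening history or intention measure and plans no adjustment for one, so own screening intention pools women who have already stopped with women still screening, at a cost in precision and dilution but not bias.

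*Protocol*

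**What the plan says.** Section C.5 of the protocol measures own intention with one item, "How likely is it that you will get a mammogram in the next two years", scored as "1=very likely to get a mammogram, 7=very unlikely to get a mammogram". Table 2 lists "Screening intention for oneself" as secondary, measured at Wave 1 and Wave 2 in all six groups. It shows no assessment before the Wave 1 message.

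Section B ties Aim 3 to this outcome: the focus groups will work on "the messages from Aim 2 that most effectively reduced screening intentions".

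Three places could have separated women who have stopped from women still screening. None does:

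- **Eligibility (C.3):** "Inclusion criteria: 65 years; female; part of KnowledgePanel; able to complete survey in English". The only question named as coming at the start of the survey is the breast cancer screener: "We will independently include a screening question at the beginning of the survey regarding breast cancer history".
- **Allocation (C.2):** "participants will be sorted by the randomly generated numbers and by race/ethnicity, geographic region, education".
- **Analysis (C.6):** an ANOVA of mean scores with a multiplicity adjustment, plus "exploratory analyses by key covariates, including age, predicted life expectancy based on health and functional status".

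**The concern.** With no condition on screening status, the sample will contain women who no longer have mammograms alongside women who still do. The first group can sit at or near 7 before reading anything, and a stop message cannot raise a score of 7. Two things follow for own intention at Wave 2. The gap between the two kinds of women stays in the error term, and the average effect of a stop message is diluted by women who have no room to move in that direction.

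The Wave 1 score does not solve this. Table 2 has no pre-message time point, and the awareness items in C.5 allow for information met during the survey itself. Wave 1 outcomes in Groups 2-6 therefore appear to be taken after the message, so using them as a baseline would adjust for part of the effect under study.

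The outcome matters although it is secondary. Section B states the Aim 2 hypothesis on intentions, C.6 states the conflicting-message hypothesis (Groups 5 and 6) on intentions alone, and Aim 3 selects messages on it. The power statement in C.6 covers only the primary vignette outcome.

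**Working it through.** **1. The plan's own figures.** From C.6: 400 per group at Wave 2, 80% power, a 0.30-point difference, 20% attrition.

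- Attrition: 400 / (1 - 0.20) = 500 per group, and 6 x 500 = 3000, as stated.
- Neither SD nor alpha is given, so the 80% cannot be checked independently. At two-sided 0.05 with no multiplicity adjustment, the multiplier is 1.960 + 0.842 = 2.802. The implied SD is 0.30 / (2.802 x sqrt(2/400)) = 0.30 / 0.198 = 1.51.

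**2. Spread of own intention (all inputs assumed; none is in the documents).** A share f = 10-30% has stopped, with mean 6.8 and SD 0.5. The rest have mean m = 2.0-2.5 and SD s = 1.3-1.5.

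- Within-class variance W = f x 0.5² + (1 - f) x s²
- Between-class variance B = f(1 - f)(6.8 - m)²
- Share of variance due to the split = B / (W + B)
- Detectable difference at 400 per group = 2.802 x SD x sqrt(2/400)

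Example with f = 0.20, m = 2.5, s = 1.5: W = 0.05 + 1.80 = 1.85; B = 0.16 x 18.49 = 2.96; SD = sqrt(4.81) = 2.19; share = 2.96 / 4.81 = 0.615; detectable difference = 0.43.

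Over all corners of the inputs, the total SD is 1.79-2.55, the split explains 45-79% of the variance, and the unadjusted detectable difference is about 0.355-0.505. Removing B entirely would bring the last figure to 0.22-0.28, but only if the item identified stopped women perfectly.

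**3. What an imperfect item recovers.** Time since last mammogram is a proxy for having stopped. With sensitivity and specificity both equal to q (assumed 0.80-0.90), the share testing positive is t = fq + (1 - f)(1 - q). The fraction of B captured is c = f(1 - f)(2q - 1)² / [t(1 - t)]. Then R² = c x B / (W + B), and the SE falls by 1 - sqrt(1 - R²).

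Same example:

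- q = 0.90: t = 0.26; c = 0.16 x 0.64 / (0.26 x 0.74) = 0.532; R² = 0.532 x 0.615 = 0.327; SE falls 18%.
- q = 0.80: t = 0.32; c = 0.16 x 0.36 / (0.32 x 0.68) = 0.265; R² = 0.163; SE falls 8.5%.

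| f | c at q = 0.80 | SE reduction | c at q = 0.90 | SE reduction |
|---|---|---|---|---|
| 10% | 0.168 | 3.8-4.9% | 0.390 | 9.2-11.9% |
| 20% | 0.265 | 8.5-10.1% | 0.532 | 18.0-21.6% |
| 30% | 0.321 | 12.0-13.7% | 0.599 | 23.9-27.6% |

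The overall range is about 4-28%.

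**4. Variance and dilution together.** As a second illustration, put a share p exactly at 7 and the rest at mean 3 with SD 1.51, and let a stop message shift only the rest, by 0.30. The average effect is 0.30(1 - p). The residual variance is (1 - p) x 1.51² + p(1 - p) x 4² x (1 - c). Power at 400 per group, two-sided 0.05:

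| p | Average effect | Unadjusted | q = 0.80 | q = 0.90 | Perfect item |
|---|---|---|---|---|---|
| 10% | 0.27 | 53.2% | 56.1% | 60.5% | 75.8% |
| 20% | 0.24 | 36.7% | 42.1% | 49.6% | 70.8% |
| 30% | 0.21 | 26.5% | 32.5% | 40.8% | 65.0% |

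Even the perfect item stays below 80%, because adjustment removes variance and does not undo dilution.

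**5. Primary vignette outcome.** With an assumed R² of 0.05-0.10, the SD of 1.51 becomes 1.51 x sqrt(1 - R²) = 1.48-1.44. The detectable difference moves from 0.30 to 0.29-0.28, and power at 0.30 from 80% to 82-84%.

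**The case against.** A reader might infer that no screening history is collected at all. The protocol does not say so. C.5 lists outcome items, not the whole questionnaire: the health and functional status items that C.6 needs for life expectancy are not listed either. The covariate list in C.6 is open-ended, and C.2 and C.3 say the panel already holds member data. What can be said is that the protocol names no such measure and plans no adjustment for it.

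A reader might also infer that women who have stopped cannot respond. That is true in one direction only. A woman at 7 can move down after a continue message, which is what Groups 5 and 6 read at Wave 1, so she is informative for the conflicting-message hypothesis.

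A third inference is that the group comparison is biased. It is not: allocation is randomised, and an unadjusted comparison of means is valid for the whole sample.

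It can further be argued that covariates for a secondary outcome belong in the SAP, which is not at hand. That is fair for the choice of model term. It does not cover collection, since an SAP can adjust only for what was measured, and a clean pre-message answer cannot be recovered after exposure.

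Finally, asking about a woman's own mammogram just before the message may anchor her answer on own intention. Equal exposure across groups prevents imbalance but does not rule out a smaller message effect. This stands as a modest cost.

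**Conclusion.** The point holds as a cheap improvement to a secondary outcome, not as an error that threatens the trial. Nothing in eligibility, the allocation sort, Table 2 or the stated analysis separates women who have stopped from women still screening, and Wave 1 appears to come too late to serve as a baseline in Groups 2-6. The consequence is a noisier own-intention comparison and a diluted stop-message effect, on the outcome that Aim 3 will use.

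The size is uncertain. With 10-30% already stopped and an item of 80-90% sensitivity and specificity, the standard error falls by roughly 4-28%. The share stopped, the means, the SDs and the item's accuracy are all assumptions. Detectable differences as low as 0.22-0.28 should not be expected, because they need near-perfect classification. For the primary outcome the gain is small. Severity is minor and confidence in the magnitude is low.

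**What to change.** - **C.3:** beside the breast cancer screener, and before any message, ask when the last mammogram was (within two years, longer ago, never). If the panel already holds this, take it from its records, which avoids priming.
- **C.6:** prespecify the variable as a covariate in the Wave 2 model for own intention, and optionally for support for cessation. Report own intention by recent versus no recent mammogram as a prespecified exploratory subgroup. The subgroup report is needed as well as the covariate, since adjustment does not show the effect in women with room to move.

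The cost is one question, one model term and possibly slight priming, equal across the six groups. If the questionnaire already contains the item, only the C.6 change is needed.

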#### **C.6. Statistical methods and sample size.**

The main analysis focuses on the primary outcome assessed at Wave 2 with the independent variables being the randomly assigned message/messenger combinations. The primary goal is to compare the experimental groups (Groups 3-6) at Wave 2 with both control groups to assess the combined effect of consistent and conflicting messages over time. We hypothesize that the participants who read consistent messages both directed at reducing over-screening (Groups 3,4) will have higher support and higher intentions to stop screening than participants who read clinician message alone (Group 2); the participants who read conflicting messages (Groups 5,6) will have lower intentions to stop screening than participants who read clinician message alone (Group 2). We will compare the mean scores across groups using ANOVA and adjust for multiple comparisons. We will conduct exploratory analyses by key covariates, including age, predicted life expectancy based on health and functional status, to examine the impact of messaging within these subgroups.

Power calculations are based on preliminary data in which we asked 41 patients 65+ about willingness to stop routine cancer screening if recommended by their clinician. Based on the distribution of responses from this preliminary data, we estimate that with 400 participants randomized to each group at Wave 2, we will have 80% power to detect a 0.30 point difference for the primary outcome. The survey company Ipsos that manages and maintains the KnowledgePanel affirms that, through their recruiting strategy and based on their past experience, 20% attrition or less is expected between the two waves over 1-2 weeks. Assuming 20% attrition, we will target 500 per group at Wave 1.

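### The main analysis in C.6 compares Wave 2 means only and, as stated, makes no use of the primary-outcome score recorded at Wave 1 in all six groups

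*Protocol*

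**What the plan says.** Section C.6 fixes three things.

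- **Time point:** "The main analysis focuses on the primary outcome assessed at Wave 2".
- **Estimator:** "We will compare the mean scores across groups using ANOVA and adjust for multiple comparisons".
- **Sample size:** "with 400 participants randomized to each group at Wave 2, we will have 80% power" for a difference of 0.30 points. The survey company's figure is that "20% attrition or less is expected between the two waves over 1-2 weeks", and therefore "Assuming 20% attrition, we will target 500 per group at Wave 1".

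In Table 2 (C.5), the row "Support for screening cessation for hypothetical patient" is marked at both waves for every group. Table 1 (C.4) shows that Groups 2 to 6 read their first message at Wave 1: a stop message in Groups 2, 3 and 4, and a continue message in Groups 5 and 6. Group 1 reads nothing. Any loss between waves therefore comes after the groups have been treated differently.

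In C.6, attrition enters only as an inflation of the sample size.

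**The concern.** Taken as written, an ANOVA of Wave 2 scores is an analysis of the women who return. Returning is a post-randomisation event, and the Wave 1 message could influence it. If women who dislike what they read come back less often, the Wave 2 means are no longer a clean randomised comparison. Enlarging the groups from 400 to 500 protects power but does nothing about this.

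The direction matters for one hypothesised contrast. High scores mean support for stopping. Women who reject a stop message tend to be low scorers, so losing them raises the Group 2 mean. Women who reject a continue message tend to be high scorers, so losing them lowers the means of Groups 5 and 6. Both shifts would push the comparison of Groups 5 and 6 with Group 2 in the hypothesised direction, and equal drop-out rates would not reveal it.

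The Wave 1 score is information on exactly this selection. It will already be in the data, and it also carries some precision about Wave 2.

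**Working it through.** **1. The plan's own figures.** 400 / (1 − 0.20) = 500 per group. 6 × 500 = 3000 women at Wave 1, which agrees with the total in section B, and 6 × 400 = 2400 at Wave 2. These reproduce exactly. At the upper bound of attrition, up to 3000 − 2400 = 600 women would fall outside a Wave 2 comparison.

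**2. The SD.** The protocol gives neither SD nor alpha. Assuming two-sided alpha 0.05 and inverting the two-means formula:

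SD = 0.30 / [√(2/400) × (1.960 + 0.842)] = 0.30 / (0.0707 × 2.802) ≈ 1.51.

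This value is back-solved, not stated. The standard error of a two-group Wave 2 difference is then 1.51 × √(2/400) ≈ 0.107.

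**3. Precision under random loss.** With 20% missing completely at random and correlation ρ between waves, the variance of a Wave 2 mean estimated from both waves, relative to returners only, is 1 − 0.20ρ².

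- ρ = 0.5: 1 − 0.20 × 0.25 = 0.95
- ρ = 0.6: 1 − 0.20 × 0.36 = 0.93
- ρ = 0.7: 1 − 0.20 × 0.49 = 0.90

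The variance falls by 5 to 10%, and the standard error by about 2.5 to 5%.

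**4. Bias, general form.** If 20% are missing in one group and returners differ from non-returners by D points, that group's Wave 2 mean shifts by 0.20 × D. If drop-out in the comparison group is unrelated to outcome, D = 0.25, 0.5, 1.0 and 1.5 give 0.05, 0.10, 0.20 and 0.30 points, which is 17%, 33%, 67% and 100% of the target difference.

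**5. Bias when drop-out depends on the Wave 1 score.** Assume normal scores, SD 1.51, no true difference, and log-odds of drop-out linear in the Wave 1 score with the slope given per point. The shift in a group's Wave 2 mean is ρ × (mean Wave 1 score of returners − mean Wave 1 score of all). I evaluated this numerically and took the difference between two groups.

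| Scenario | Slope | ρ = 0.5 | ρ = 0.6 | ρ = 0.7 |
|---|---|---|---|---|
| Same mechanism, 20% vs 20% | 0.2 or 0.6 | 0.00 | 0.00 | 0.00 |
| Same mechanism, 18% vs 22% | 0.6 | 0.02 | 0.03 | 0.03 |
| Same mechanism, 15% vs 25% | 0.2 | 0.02 | 0.03 | 0.03 |
| Same mechanism, 15% vs 25% | 0.6 | 0.06 | 0.07 | 0.08 |
| Outcome-related in one group only, 20% vs 20% | 0.6 | 0.12 | 0.15 | 0.17 |
| Opposite directions, 20% vs 20% | 0.2 | 0.09 | 0.11 | 0.13 |
| Opposite directions, 20% vs 20% | 0.6 | 0.24 | 0.29 | 0.34 |

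Example for the last row: with slope 0.6 and 20% loss, returners lie 0.243 points from the group's Wave 1 mean. The shift is 0.6 × 0.243 = 0.146 per group at ρ = 0.6, and 2 × 0.146 = 0.29 between groups.

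In these scenarios an estimate that uses the Wave 1 score has bias of about 0.00. That follows from the set-up, because drop-out was made to depend on that score alone.

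**The case against.** Four objections deserve weight.

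- **The SAP is not shown.** A reader might infer that the plan leaves message-related drop-out uncorrected. The documents do not support that. C.6 does not say that only complete cases will be analysed, and a Wave 2 comparison is compatible with imputation or weighting set out in the SAP. What stands is narrower: the main analysis that C.6 names makes no stated use of the Wave 1 score.
- **The drop-out mechanism is assumed.** A reader might also infer that 20% will be lost and that the loss follows the message. The protocol says 20% or less. It does not say that return depends on the message, and measuring annoyance or worry does not show that they drive drop-out. Panel incentives (D.4) and a 10-minute second survey (D.2) may limit such loss. This stands.
- **The larger figures need strong selection.** A slope of 0.6 per point is an odds ratio of 1.82 per point, or about 2.5 per SD. A 25% loss in one group exceeds the stated bound if that bound applies group by group. Even 0.07 points is below one standard error (0.107). This stands, and it is why a range is given.
- **The remedy is partial.** A two-wave model of the primary item fully corrects drop-out that depends on the Wave 1 score, and only in part drop-out that depends on unseen Wave 2 values or on reactions which that score does not capture. This stands too.

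None of this makes the Wave 2-only estimator the better choice. It needs the stronger assumption about drop-out and discards data that the study collects.

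**Conclusion.** The point holds in a limited form: it is a recommended improvement to the stated main analysis, not a demonstrated bias. The loss of precision is modest, at 5 to 10% of the variance of a Wave 2 mean when 20% are lost at random, and less if fewer are lost. The bias is hypothetical. It runs from 0.00 points with the same mechanism and equal attrition, through about 0.02 to 0.08 with 15% against 25%, to about 0.1 to 0.3 if selection runs in opposite directions between groups. All of these rest on the back-solved SD, the assumed alpha of 0.05, the assumed correlation of 0.5 to 0.7, and the assumed drop-out slopes. The plan's own sample-size arithmetic for attrition is correct.

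**What to change.** Make the main analysis a repeated-measures linear mixed model on both waves in all women who answered the primary item at Wave 1, with group, wave, group-by-wave interaction and an unstructured covariance. Take from it the same multiplicity-adjusted Wave 2 contrasts. Keep the Wave 2 ANOVA as a sensitivity analysis, and report attrition by group.

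Do not enter the Wave 1 score as an ordinary baseline covariate. In Groups 2 to 6 it appears to be taken after the message (the item order is not stated), so adjusting for it could remove part of the message effect.

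The cost is a change of wording in C.6 and slightly more analysis work, with no new data or participants. The downside is reliance on missing-at-random given the Wave 1 score. That is a weaker assumption than the returners-only comparison needs, but it leaves drop-out driven by unseen Wave 2 values only partly corrected. If the SAP already specifies such an analysis, C.6 need only be brought into line with it.
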